## Abstract

**Background:**

Subjective cognitive impairment (SCI), the earliest sign of cognitive decline, affects 1 in 9 Americans aged older than 45 years. It negatively affects quality of life and is a risk factor for dementia. Healthy eating is a primary preventative strategy to impede cognitive decline. In the short term, cognitive function may be impacted by the consumption of a single meal, suggesting that the meal components, and not solely the metabolic dysregulation resulting from the condition of obesity, can impact cognition. The effect of meals on postprandial cognitive function is influenced by their macronutrient composition. A meal with a low-quality fat composition can acutely impair postprandial cognitive function. Walnuts are a source of high-quality fat as well as polyphenols. Some randomized control trials have shown that walnuts may benefit cognitive function. However, it is not clear whether a single meal high in walnuts can improve cognition in adults with SCI.

**Objective:**

The primary objective of the Essential Fats for Enhancing Cognitive Thinking study is to determine the impact of walnuts on postprandial cognitive function in adults with SCI. Secondary objectives include assessing the impact of daily walnut consumption for 1 week on cognitive function and erythrocyte fatty acids. Exploratory objectives include understanding the effect of walnut consumption on microbiota and intestinal inflammation.

**Methods:**

In this 7-week single-blind randomized crossover design study, 78 adults with SCI consumed 1 study snack per day, consisting of walnuts or a chocolate-style snack for 1 week, with a 4-week washout period between. Before consuming each study snack, participants underwent a meal challenge that included this study’s snack. Before randomization, participants completed a 1-week run-in period to become acclimated to consuming 1 study snack per day. A registered dietitian nutritionist counseled participants on incorporating this study’s snack into their diet while maintaining their body weight. Participants were blinded to which snack was the treatment and which was the control. Dietary intake and physical activity were measured with 24-hour recalls. Cognitive function was measured using the National Institutes of Health Toolbox for the Assessment of Neurological and Behavioral Function Cognitive Battery, both pre- and postprandially, as well as after 1 week of study snack consumption. Stool samples were collected weekly, except during the washout period, to measure microbiota α-diversity, β-diversity, and butyrate. Additionally, fasting blood samples, weight, and waist circumference were obtained at each study visit.

**Results:**

Recruitment began in February of 2024 and was completed by May 31, 2025.

**Conclusions:**

Improving cognition through the consumption of walnuts may ultimately prove to be an effective way to mitigate SCI.

**Trial Registration:**

ClinicalTrials.gov NCT06223672; https://clinicaltrials.gov/study/NCT06223672

**International Registered Report Identifier (IRRID):**

DERR1-10.2196/82032

## Introduction

### Background

Cognitive decline ranges from subjective cognitive complaints to mild cognitive impairment to diagnosed dementia. Subjective cognitive impairment (SCI) is the earliest sign of cognitive decline and consists of the experience of worsening or more frequent confusion or memory loss in the absence of observable functional decline [1]. Affecting 1 in 9 Americans aged older than 45 years, SCI is associated with mental distress and poses a risk for dementia [2-4]. Most people with SCI do not progress to a diagnosis of dementia, but some do. In a large US longitudinal cohort study, subjective cognitive decline occurred 4.4 years before mild cognitive impairment, 6.8 years before Alzheimer disease, and 6.9 years before all-cause dementia [5]. Even though the polygenic risk score did not differ between those with subjective cognitive decline and those without it, the former had more than double the risk of developing dementia (hazard ratio 2.14, 1.44-3.18). There are currently no treatments available for dementia; therefore, focusing on prevention strategies at the earliest sign of increased risk—when subjective complaints are present—is important [6].

Healthy eating is a primary preventative strategy for impeding cognitive decline [7,8]. The DASH (Dietary Approaches to Stop Hypertension) diet has been associated with a lower prevalence of subjective cognitive complaints [9]. Additionally, the Mediterranean-style diet and the Mediterranean–Dietary Approaches to Stop Hypertension Intervention for Neurodegenerative Delay diet have been associated with slower cognitive decline in older adults [10-12]. Furthermore, higher Mediterranean diet adherence has been associated with lower odds of having SCI [13,14]. The Mediterranean-style diet features foods rich in unsaturated fats, including sources of the essential fatty acids, α-linolenic acid (ALA) and linoleic acid (LA), as well as polyphenols such as flavonoids and tannins.

Chronic intake of saturated fat, on the other hand, is associated with poorer cognition and the risk for cognitive decline [15-17]. Even in the shorter term, 4 to 7 days, consumption of a high saturated fat diet can affect cognitive function [18-21]. Shorter still, the fat content of a single meal may impact cognitive function [22-28]. In adult males and females, after consuming a meal high in saturated fat, cognitive function is negatively impacted compared to a meal high in unsaturated fats [22,23]. Polyunsaturated fatty acids, on the other hand, may have a beneficial effect on cognitive function [29]. As a rich source of the polyunsaturated fatty acids ALA and LA, consumption of walnuts is associated with a lower risk of cognitive decline [30] and can influence postprandial cognitive function. In healthy, young adults, a high-fat breakfast featuring walnuts improved executive function and initially decreased, but later in the day increased, memory recall compared to a breakfast featuring butter [28]. However, the effect of walnut consumption on postprandial cognition in adults with SCI has not been examined.

The exact mechanism for the potential beneficial effects of walnuts on cognitive function is not known. Potential mechanisms include altering the gut microbiota by increasing β-diversity and shifting relative bacterial populations [31,32], or altering inflammation through metabolism of ellagitannins found in walnuts, which are metabolized to form anti-inflammatory urolithins [33-35]. Additionally, ALA and LA have been shown to reduce endotoxemia and inflammation [36-40]. Conversely, saturated fats promote inflammation, which negatively impacts cognitive function [41,42]. Both saturated and unsaturated fatty acids cross the blood-brain barrier, but this is not always detrimental; in moderation, saturated fatty acids may promote brain health and development [43,44]. Even without crossing the blood-brain barrier, fatty acids can impact the brain via inflammation. Saturated fats, which closely resemble the lipid portion of the endotoxin lipopolysaccharide, stimulate signaling via toll-like receptor-4 [45], an effect that mimics lipopolysaccharide’s effect [46]. Activation of toll-like receptor-4 stimulates production of proinflammatory cytokines that cross the blood-brain barrier, which causes neuroinflammation [47]. Saturated fats can also promote inflammation in the gastrointestinal tract, which increases intestinal permeability. A permeable intestine allows bacterial components such as lipopolysaccharide to escape into the bloodstream. Both lipopolysaccharide and saturated fats are powerful provocateurs of the inflammatory response, shifting the microbial composition and leading to a potentially unstable, imbalanced state, which further exacerbates proinflammatory signaling, resulting in a vicious cycle [15]. Additionally, lipopolysaccharide has been negatively associated with cognitive function [15]. Therefore, both chronic and acute dietary fatty acid consumption may influence cognition.

### Objectives

The objectives of the Essential Fats for Enhancing Cognitive Thinking (EFFECT) study are to (1) determine the impact of walnuts on postprandial cognitive function, and (2) assess the impact of daily walnut consumption for 1 week on cognitive function, the microbiota, and intestinal inflammation in adults with SCI.

## Methods

### Study Design and Setting

The EFFECT study was a 7-week randomized single-blinded placebo-controlled crossover design study. This study consisted of a 1-week run-in period followed by two 1-week intervention periods separated by a 4-week washout period. All participants were asked to consume 1 study snack per day throughout this study, except during the washout period. After completing the run-in period, participants were randomly assigned to the order of snack consumption: control snack followed by walnut snack or walnut snack followed by control snack. All study visits took place at The Ohio State University (OSU).

### Recruitment

A total of 78 adults with SCI were planned to be recruited from the central Ohio area. Inclusion and exclusion criteria are reported in Textbox 1. Study flyers were placed around the OSU campus and off-campus sites that include community centers, libraries, restaurants, and coffee shops. Additionally, study flyers were distributed to outpatient medical clinics in the Columbus, Ohio area. Potential participants were sent information about this study through The Ohio State Wexner Medical Center’s MyChart, and those who agreed to release their information to the research team were prescreened for eligibility. Radio advertisements were placed to reach potential participants outside of the OSU community. Recruitment for this study included or was carried out via ResearchMatch, a national health volunteer registry that was created by several academic institutions and supported by the US National Institutes of Health as part of the Clinical Translational Science Award program. ResearchMatch has a large population of volunteers who have consented to be contacted by researchers about health studies for which they may be eligible.

Inclusion and exclusion criteria.
**Inclusion criteria**
Subjective cognitive impairment assessed as a score of ≥4 on either item of the Kohli scaleAge 40-75 yearsBMI ≥20 kg/m^2^
**Exclusion criteria**
Montreal Cognitive Assessment score of <23Diagnosis of mild cognitive impairment or dementiaCurrent diagnosis of or current treatment of cancer other than nonmelanoma skin cancer or chronic stable cancersGastrointestinal or pancreatic diseases or disorders where consumption of this study’s snacks would be contraindicated or not tolerated, or nutrient absorption would be impairedBariatric or gastric bypass surgeryHyperthyroidism diagnosisFood allergy or intolerance or dietary restrictions, or use of supplements or medications, where consuming study snacks is contraindicatedUse of supplements high in linoleic acid or α-linolenic acid in the 4 weeks before enrollingPregnancy and lactationPsychostimulant or nootropic medication useCurrent use of supplements or medications for weight loss or following a weight loss programSevere or uncontrolled autoimmune diseases (excluding rheumatoid arthritis, psoriasis, and lupus)Current or previous diagnosis of severe kidney failure (glomerular filtration rate <30), liver cirrhosis, and some pulmonary diseases (ie, chronic obstructive pulmonary disease and emphysema)Heart disease events (including stroke or heart attack) within the last 3 months before enrollmentAlcohol or drug abuse

Before providing informed consent, this study’s team screened potential participants over the phone using this study’s screening questionnaire to confirm that participants were likely eligible for this study. Those who passed the phone screening questionnaire and preferred to enroll in this study provided written informed consent before completing an in-person screen. The in-person screen consisted of measuring height and weight to calculate BMI, and completion of the Montreal Cognitive Assessment. Participants who passed the in-person screen began this study.

### Study Timeline

The EFFECT study duration was 7 weeks and consisted of 5 study visits (Figure 1). Participants were asked to fast overnight for at least 12 hours before each study visit. Participants reported to the OSU campus for their in-person screening. Those who passed the in-person screen stayed and completed their first study visit (week –1), the start of the run-in period. During their week –1 visit, participants filled out the baseline questionnaire and listed their current medications and supplements. Blood pressure, pulse, temperature, and waist circumference were measured, as well as dominant hand grip strength. A finger stick and venous blood draw were also completed. The run-in period lasted 1 week and concluded with their week 0 study visit.

**Figure 1 figure1:**
[figure not shown]
Study timeline.

At the beginning of each intervention period (weeks 0 and 5), participants reported to the Clinical Research Center on the OSU campus. At the Clinical Research Center, weight, vitals, and waist circumference were measured, sleep and diet questionnaires were answered, fasting indirect calorimetry was completed, a fasting blood draw was collected, and the meal challenge was administered with subsequent blood draws and indirect calorimetry measurements performed hourly for 5 hours. Additionally, cognitive function was measured both fasting and at 5 hours after the meal challenge, and any updates to medications and supplements were recorded. Each intervention period lasted 1 week and concluded with a study visit (week 1 and week 6). At the week 1 and week 6 visits, weight, vitals, and waist circumference were measured. A fasting blood draw was collected, cognitive function was measured, and updates to medications and supplements were obtained. There was a 4-week washout period between intervention periods. Figure 2 describes the measurements and information collected at each study visit. Participants were supplied with enough study snacks to consume 1 study snack per day until their next study visit. No study snacks were consumed during the washout period. At study visits, this study’s team verbally asked participants about adherence to consuming 1 study snack per day, changes to diet or activity, and changes to medications or supplements.

**Figure 2 figure2:**
[figure not shown]
Study measurement timeline. ACT24: Activities Completed Over Time in 24 Hours; ASA24: Automated Self-Administered 24-Hour; CES-D: Center for Epidemiologic Studies Depression Scale; HbA1c: glycated hemoglobin; MoCA: Montreal Cognitive Assessment; NIHTB-CB: National Institutes of Health Toolbox for the Assessment of Neurological and Behavioral Function Cognitive Battery. *These were not administered at this study’s visits. They were given a total of 3 times during the study, which occurred between the week 0 visit and the week 6 visit. The intent is to capture snapshots of diet and activity during the beginning, middle, and end of the study. The “-----------------------" is meant to indicate that the measurement could occur at any time during this range.

### Randomization

Participants were randomly assigned to the order of snack consumption: control followed by walnut or walnut followed by control. A statistician or graduate student studying statistics outside the clinical research team generated the randomization schemes in blocks of 2 and 4. After participants completed the week –1 study visit and before they completed their week 0 visit, the product coordinators assigned participants to the order of intervention from the randomization schemes. The product coordinators also prepared the snacks and meals for distribution to the participants, but had no interaction with the participants.

### Interventions

Participants were asked to consume 1 study snack per day throughout this study except during the washout period. Study snacks were portioned at the OSU research kitchen. At weeks –1, 0, and 5, participants were given enough portions of snacks to consume 1 portion per day until their next study visit. Participants were able to choose which time of day and whether to consume the whole portion at once or split it throughout the day. To avoid weight gain, this study’s dietitians worked individually with each participant to incorporate this study’s snack into their diet by replacing similar foods they were already consuming with this study’s snacks. All participants received instructions for incorporating this study’s snack into their diets and a list of typical foods to replace with this study’s snack. During the run-in period (week –1), participants consumed 1 study snack per day consisting of a brownie-style white chocolate snack (Eating Evolved; Table 1). During 1 intervention period, participants consumed a control snack consisting of a white chocolate-style bar (Eating Evolved). During the other intervention period, participants consumed walnuts.

**Table 1 table1:** Study snack nutrition information^a^.

	1 Serving (g)	Energy (kcal)	Fat (g)	Saturated fat (g)	MUFA^b^ (g)	PUFA^c^ (g)	Carbohydrates (g)	Sugar (g)	Fiber (g)	Protein (g)
Run-in period snack	67	369	34	11	17	4	23	3	10	7
Walnuts	56	366	37	3	5	26	8	1	4	9
White chocolate-style bar	68	366	34	15	15	3	24	2	17	5
Alternate run-in snack	73	364	31	13	—^d^	—	29	3	10	8
Alternate control snack	75	375	35	18	—	—	25	3	7	10

^a^Monounsaturated fatty acid and polyunsaturated fatty acid information was not available for alternate snacks.

^b^MUFA: monounsaturated fatty acids.

^c^PUFA: polyunsaturated fatty acids.

^d^Not available.

Due to unforeseen supply chain issues, which eliminated access to snacks, an alternate run-in period snack consisting of chocolate-covered peanuts (Lakanto, Saraya USA, Inc) and an alternate control snack consisting of dark chocolate peanut butter cups (Lakanto) were used. Alternate snacks were chosen based on matching energy, macronutrients, and saturated fat to the original run-in and control snacks as closely as possible. All study snacks had no added sugar.

The nutrition information of this study’s snacks is provided in Table 1. Participants were provided with nutrition information on all snacks during this study.

During this study, participants were asked to maintain their normal physical activity and eating patterns except for replacing a similar habitual food with this study’s snack and removing foods high in ellagitannins and replacing them with similar foods low in ellagitannins.

Throughout this study, the study’s dietitians were available to help participants avoid weight gain from the study’s snacks. The goal was for participants to maintain their weight for the entire study. Weight maintenance was considered at ≤±2 kg over 2 weeks. This study’s dietitians discussed with the participant potential reasons for weight change and adjusted counseling as needed. Participants were able to choose which time of day they consumed this study’s snack, and whether it was consumed as part of a meal or as a snack. The participants chose whether to consume this study’s snack all at once or spread the portion out over the course of the day. The participants were asked to record the study snack they consumed each day and the relative time of day this study’s snack was consumed (morning, afternoon, evening, etc). Participants were asked to return uneaten study snacks at their next study visit.

### Blinding

The EFFECT study was single-blinded. Participants were not told which snack was the treatment and which was the control. The researchers told participants that 2 snacks were being investigated, but did not disclose the hypothesis of this study to participants. Due to the nature of this study, it was not possible to blind the research team. Once all participants completed this study, they received information about which study snack was the treatment and which study snack was the control. As the snacks were not blinded to the participants or the clinical study team, there was no testing of blinding success.

### Outcomes

#### Cognitive Function

The primary outcome of the EFFECT study is the difference in postprandial cognitive score between control and walnut interventions. Additionally, the difference in change of premeal score at the start and end of the intervention period between the control and walnut interventions will be analyzed. To assess cognitive function, the National Institutes of Health Toolbox for the Assessment of Neurological and Behavioral Function Cognitive Battery (NIHTB-CB) was used, specifically the fluid cognition battery. The tests are fully automated and administered via an iPad (Apple Inc) with consistent program-derived instructions. Minimal practice effects and no floor or ceiling effects are seen with the NIHTB-CB [48-50].

#### Microbiome

Participants were instructed to collect a stool sample on the 1-2 days before or the morning of week 0, 1, 5, and 6 study visits. An Omnigene Gut fecal collection kit (OMR-200, DNAGenotek) was provided with specific instructions for how to store the sample until delivery to the clinic. Total DNA will be isolated using QIAGEN Power Fecal Pro kits and sequenced to a depth of >25 million reads per sample. Microbe or gene abundances will be defined via alignment to reference genomes and de novo assembly.

#### Anthropometrics

Waist circumference was measured at each study visit using a nonstretch tape measure at the uppermost border of the right iliac crest. Weight and height were measured without shoes using a digital scale and a stadiometer, respectively. Weight was measured to the nearest 1 kg, and height was measured to the nearest 0.1 cm. Weight was measured at each study visit, and height was measured at the first study visit. Height and weight were used to calculate BMI. Grip strength was measured at the first study visit using a Jamar handheld dynamometer and reported in kilograms as previously described [51].

#### Meal Challenge

At weeks 0 and 5, participants received a high-kilocalorie meal challenge. The meal was approximately 900 kcal with 60 g of fat, 33 g of polyunsaturated fat for the walnut meal and 41 g of saturated fat for the control meal, 60 g of carbohydrates, and 37 g of protein; the meal consisted of a drink and the corresponding intervention period study snack. The macronutrient composition of the meals between the 2 study snacks was equivalent except for the saturated fat, monounsaturated fat, and polyunsaturated fat content. Participants had 20 minutes to consume the entire meal. To measure preprandial and postprandial metabolism, before consuming the meal (fasting) and each hour for 5 hours after consuming the meal, energy expenditure, blood pressure, and heart rate were measured, and venous blood samples and saliva samples were collected.

Energy expenditure was measured using indirect calorimetry (Ultima Series CPX, MGC Diagnostics). For the fasting indirect calorimetry, after arriving for their study visit, participants rested in a quiet, dim room on a hospital bed with the head of the bed at a 30° angle for 30 minutes before assessing energy expenditure over 25 minutes. For postprandial measurements, participants rested for 30 minutes in a hospital bed while being allowed to quietly read, use electronics, or sleep before a 20-minute indirect calorimetry measurement period. A heart rate monitor (FirstbeatTM Bodyguard 3, Firstbeat Technologies) was placed on the participant’s chest and abdomen at the start of the first resting period and measured their heart rate throughout this study’s visit. Fasting and postprandial blood pressure were measured using a blood pressure cuff.

To reduce variability in postprandial measurements, participants were provided with all meals and snacks for the day before the meal challenge [52]. As described in prior research, the meals and snacks were approximately 30% fat, 20% protein, and 50% complex carbohydrate with low added sugars [53,54] and were prepared by the Ohio State Clinical Research Center. To further reduce variability of postprandial measurements, participants were also instructed to avoid taking blood pressure, glucose-lowering, lipid or cholesterol-lowering, and nonsteroidal anti-inflammatory medications the morning of the meal challenge, to avoid alcohol the day prior, to avoid strenuous exercise 2 days prior, and to abstain from taking dietary supplements and aspirin for 7 days before the meal challenge.

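### The stated meal-challenge fat figures cannot come from one common drink plus the Table 1 snacks: either a figure is wrong, or the drink fat differed by arm and the primary difference is not attributable to walnuts alone

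*Protocol article*

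**What the plan says.** All places are in the protocol article.

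- **Objectives.** The first aim is to "determine the impact of walnuts on postprandial cognitive function". The primary outcome (Outcomes, Cognitive Function) is the control-versus-walnut difference in postprandial score.
- **Meal Challenge.** "The meal was approximately 900 kcal with 60 g of fat", with "33 g of polyunsaturated fat for the walnut meal and 41 g of saturated fat for the control meal". On components: "the meal consisted of a drink and the corresponding intervention period study snack". On comparability: "The macronutrient composition of the meals between the 2 study snacks was equivalent except for the saturated fat, monounsaturated fat, and polyunsaturated fat content". Nothing there says whether the drink was the same in both arms.
- **Interventions, Table 1.** One serving of walnuts has 37 g fat (3 g saturated, 5 g monounsaturated, 26 g polyunsaturated). The white chocolate-style bar has 34 g (15, 15 and 3 g). The alternate control snack has 35 g, 18 g of it saturated, with the other two classes not available.
- **Discussion, Comparison With Prior Work.** The trial is set apart from earlier oil-based meals: it is said to use no dietary oils and to provide the unsaturated fat through walnuts.
- **Sample Size.** The SD of 11.0 comes from an earlier comparison of an unsaturated-fat meal with a saturated-fat meal.

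**The concern.** A reader who takes the two snacks as the only difference between the meals would credit the whole primary contrast to walnuts. The stated meal totals do not allow that reading, because the fat left over for the drink is of a different kind in each arm.

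This matters because the article's own Background and Discussion report worse cognition after saturated-fat meals than after unsaturated-fat meals. If the control drink added saturated fat that the walnut drink did not, a difference in score would mix two things: what walnuts do, and what the extra saturated fat in the control drink does. The objective and the Abstract's conclusion speak only of the first. If instead a figure is misprinted, the description of the primary intervention is wrong and should be corrected before results are read against it.

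**Working it through.** **Check of the stated meal.** Energy = 60 × 9 (fat) + 60 × 4 (carbohydrate) + 37 × 4 (protein) = 928 kcal, which fits a meal of approximately 900 kcal. The totals are plausible as a set.

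**Drink = stated meal minus one Table 1 serving (g).**

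| | Total fat | Stated class | Consequence |
|---|---|---|---|
| Control drink (bar) | 60 − 34 = 26 | saturated 41 − 15 = 26 | all drink fat saturated, no polyunsaturated |
| Control drink (alternate snack) | 60 − 35 = 25 | saturated 41 − 18 = 23 | at most 2 polyunsaturated |
| Walnut drink | 60 − 37 = 23 | polyunsaturated 33 − 26 = 7 | at most 23 − 7 = 16 saturated |

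**Could one drink serve both meals?** It would need at least 26 + 7 = 33 g of fat. The meals would then contain at least 37 + 33 = 70 g (walnut) and 34 + 33 = 67 g (control), not 60 g. With the alternate snack the drink needs 23 + 7 = 30 g, giving 67 g and 65 g.

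**Rounding.** Let every stated meal fat figure be off by up to t, all in the helpful direction. A common drink needs (26 − t) + (7 − t) ≤ 23 + t, so t ≥ 10/3 ≈ 3.3 g. With the alternate snack, (23 − t) + (7 − t) ≤ 23 + t gives t ≥ 7/3 ≈ 2.3 g.

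**Portion size.** Suppose the portions in the meal are free and the drink has F g of fat. The portions are (60 − F)/37 servings of walnuts and (60 − F)/34 of the bar. The drink's required saturated plus polyunsaturated fat, minus F, is

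41 − 15(60 − F)/34 + 33 − 26(60 − F)/37 − F ≈ 5.4 + 0.14F,

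which is above zero for every F, so no portion size works. With the alternate snack (18/35 in place of 15/34) it is about 1.0 + 0.22F, also above zero. A linear-programming check with free portions finds no common drink when each figure may be off by 2 g (1 g with the alternate snack). It does find one at 3 g (2 g).

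**How large would a single misprint have to be?** Keep the walnut drink (23 g fat, at most 16 g saturated) for both arms: the control meal could hold at most 15 + 16 = 31 g saturated, against the stated 41 g. Keep the control drink for both arms: the walnut meal would hold 26 g polyunsaturated, against the stated 33 g.

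**Size of the contrast if the drinks differed.** The walnut meal's saturated fat is not given, so it is a range: 3 + (0 to 16) = 3 to 19 g.

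- Saturated contrast: 41 − 19 = 22 g to 41 − 3 = 38 g.
- From the snacks (bar): 15 − 3 = 12 g.
- From the drinks: 10 to 26 g, that is 10/22 = 45% to 26/38 = 68%.
- With the alternate snack: snacks 18 − 3 = 15 g; drinks 7 to 23 g, that is 7/22 = 32% to 23/38 = 61%.
- Polyunsaturated contrast (bar): 33 − 3 = 30 g, of which the snacks give 26 − 3 = 23 g (77%) and the drink 7 g (23%).

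**The case against.** - **The documents do not say which explanation is true.** This stands. A control drink whose fat is entirely saturated is an extreme solution, so a misprint is a live possibility. On the other hand, 41 g plus the bar's 15 g monounsaturated and 3 g polyunsaturated makes 59 g, close to the stated 60 g, so the figure is at least self-consistent. What is established is a discrepancy, not a proven design flaw.
- **The difference in fat classes is disclosed.** It is, in Meal Challenge, and Sample Size and the Discussion place the trial beside saturated-versus-unsaturated meal studies. But the disclosure ties the difference to the two snacks and is silent on the drink. The Discussion's account of walnuts providing the unsaturated fat is hard to square with 7 g of polyunsaturated fat beyond the walnut serving.
- **A drink recipe belongs in the full protocol.** Agreed. The point is not that the recipe is absent, but that the printed figures do not fit together with one drink.
- **The figures are approximate.** True of the energy figure at least. The required errors of about 3.3 g (2.3 g) in every fat figure, all aligned, are more than rounding to the gram would give.
- **Carbohydrate.** A reader might infer that the drinks must also differ by 24 − 8 = 16 g of carbohydrate. That is not established. Net of fibre the snacks have 24 − 17 = 7 g and 8 − 4 = 4 g, a 3 g gap. The bar's stated 366 kcal is nearer the net count (34 × 9 + 5 × 4 + 7 × 4 = 354) than the gross one (34 × 9 + 5 × 4 + 24 × 4 = 422). Meal Challenge does not say whether its 60 g includes fibre.

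**Conclusion.** The inconsistency holds. The stated meal fat figures and Table 1 cannot both be right with one common drink, and neither rounding to the gram nor the choice of snack portion removes the conflict. Either a stated figure is wrong or the drink fat differed by arm.

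In the second case, 10 to 26 g of a 22 to 38 g saturated-fat contrast (45% to 68%, with the bar) and about 7 g of a roughly 30 g polyunsaturated contrast come from the drinks. The primary postprandial difference could then not be attributed to walnuts alone.

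Two stronger readings are tempting and are not supported. One is that the trial cannot show any impact of walnuts: walnuts supply 26 of the 33 g of polyunsaturated fat in their meal, and the snacks account for most of that contrast. The other is that a positive result would come entirely from saturated fat in the control drink: no figure in the article links grams of saturated fat to score, and its Discussion reports the harm in men only among those who were obese.

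Assumptions: the sizes take one Table 1 serving per meal and give the walnut meal's unstated saturated fat as a range. The 1-week snack comparison is not directly affected, and the sample size calculation does not depend on this point.

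**What to change.** Reconcile Meal Challenge, Table 1 and the Discussion's statement on how the unsaturated fat was supplied, and correct whichever figure or statement is wrong.

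- **If a meal figure is wrong:** correct it. The attribution problem arising from the drink then falls away, to the extent that the corrected figures fit one common drink.
- **If the drinks differed by arm:** say so, give the fat composition of each, and word the primary contrast and its conclusion as a walnut-containing unsaturated-fat meal against a saturated-fat meal, without crediting the difference to walnuts alone.

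The cost is a check of the meal records, a few sentences, and in the second case a narrower claim. No new data and no change to the analysis are needed.
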